### Strategies to improve adherence to interventions {11c}

Local principal investigators and team members are required to participate in a pre-study meeting where details of study protocol, data collection, the application, and adjustments of PEEP will be discussed. All participating centers will receive detailed written instructions. In cases of uncertainty, it will be possible to contact the Center for Pediatric Clinical Studies (CPCS, University of Tuebingen) at any time.

### Relevant concomitant care permitted or prohibited during the trial {11d}

#### Management with alternative noninvasive respiratory support (i.e., NIPPV)

NIPPV is frequently used as primary mode of noninvasive ventilation in the delivery room and the first days of life. Because the settings during NIPPV affect the applied mean airway pressure and gas exchange, NIPPV settings and weaning during the study intervention must be equally used in terms of inspiratory times, respiratory rate, and peak inspiratory pressures, which will be monitored and documented during the study intervention. We strongly recommend a center-specific protocol for the use of NIPPV prior to study initiation.

#### Caffeine therapy

Randomized infants will receive a loading dose of caffeine citrate of (10)–20 mg/kg and a maintenance dose of (5)–10 mg/kg/days. Up to 20 mg/kg/days is permitted to prevent intubation due to apnea of prematurity. Because the optimal dose of caffeine has not yet been established, exact dosing will be left to the standards of the participating centers—but centers will need to have a written dosing scheme. Furthermore, caffeine treatment will be monitored throughout the study to detect any bias in caffeine use early.

### Provisions for post-trial care {30}

Patients that are enrolled into the study are covered by patient insurance (HDI Global SE).

### Outcomes {12}

The primary outcome is meeting one of the following treatment failure criteria within the first 120 h after birth:
Need for intubation and invasive mechanical ventilation for > 1 horFiO_2_ ≥ 50% for > 1 h after NICU admissionorpCO_2_ ≥ 70 mmHg in two consecutive blood gas analyses > 2 h apart

Secondary outcomes are:
Rates of invasive or less invasive surfactant administrationCumulative dose of surfactant in mg/kg birth weightRate of intubation and invasive mechanical ventilation within the first 120 h after birthDuration of invasive mechanical ventilation within the first 120 h of life (cumulative hours)Duration of invasive mechanical ventilation until PMA36 or death (cumulative hours)Duration of any respiratory support until PMA36 or death (cumulative days)Rate and severity distribution of BPDRate of discharge with supplemental oxygenRates of postnatal systemic dexamethasone and/or hydrocortisone intended for chronic lung diseaseRate of inhaled steroidsNeed for inotropes/vasopressors within the first 120 h of lifeNeed for steroids for treatment of arterial hypotension within the first 120 h of lifeMean FiO_2_ requirements within the first 120 h of lifeMean airway pressure within the first 120 h after birth

Further outcomes are:
Bayley Scales of Infant Development (3rd) Edition at 24 months corrected ageVisual assessment at 24 months corrected ageHearing assessment at 24 months corrected ageGMFCS-Score at 24 months corrected ageWechsler preschool and primary scale of intelligence (WPPSI-III) at 60 months corrected ageLung function at 60 months corrected ageMRI of the lung and brain at 60 months

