### Objectives {7}

The primary hypothesis of this study is that the use of a higher PEEP range in preterm infants born at 26 + 0–29 + 6 weeks gestational age (GA) receiving prophylactic nasal CPAP support after birth reduces the incidence of intubation and/or meeting predefined CPAP failure criteria within the first 120 h of life when compared to the application of a lower PEEP range.

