## Statistical methods

### Statistical analysis {20a}

The following analysis populations are defined within this study:
*Intention to treat population*Consists of all patients included into the study of whom written parental consent was obtained and not withdrawn.*Safety population*The safety population is identical to the intention to treat population and consists also of all patients included into the study of whom written parental consent was obtained and not withdrawn.*Per protocol population*Patients fulfilling at least one of the following criteria will be excluded from the per protocol-population:
PEEP level is not documented or not between 3 and 5 cmH_2_O—if the infant is in the low PEEP group—or 6–8 cmH_2_O—if it is randomized in the high PEEP group—for more than 10% of time during the intervention period.Intubation within the first 10 min after birth and invasive mechanical ventilation for more than 1 h.

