The analysis of the primary endpoint will be done by Cochran-Mantel-Haenszel test stratified for treatment groups. The primary endpoint will be re-evaluated by Cochran-Mantel-Haenszel test adjusted for gestational age group (26 + 0–27 + 6 versus 28 + 0–29 + 6 weeks) and center. If the final number of centers does not allow adjustment for single centers, centers will be grouped. The grouping of centers will be justified within the statistical analysis plan. All secondary endpoints will be compared by Cochran-Mantel-Haenszel test or Student’s *t* test. In case of non-normally distributed data, Student’s *t* test will be replaced by Wilcoxon-Mann-Whitney test. The distribution of severity of BPD will be compared between the treatment groups by generalized logit model. Clinical and demographic characteristics of maternal and neonatal data will be described by mean and standard deviation, median, quartiles and minimum/maximum or rate and percentage. The analysis of the follow-up endpoints will be specified in an amendment to the study protocol before start of the 2- and 5-year follow-up. In case of more than 10% missing values concerning the primary endpoint, a worst case/best case analysis for this endpoint will be performed in the intention to treat population as sensitivity analyses and results will be included into the final report. No sensitivity analyses will be done for secondary or further relevant endpoints. In case of more than 20% missing values concerning one of the endpoints until PMA36, this endpoint will only be tabulated but no statistical test will be performed due to risk of biased data.

All analyses will be predefined in a statistical analysis plan written before end of study and completion of data monitoring. Only the analysis of the primary outcome variable in the intention-to-treat population will be considered confirmatory on a level of significance of 0.05. All other analyses including the analysis of the primary outcome variable in the per protocol population and all analyses concerning secondary endpoints will be considered exploratory only.

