### Adverse event reporting and harms {22}

The following expected serious (eSAE) and unexpected serious (uSAE) adverse events known to occur in this population of very preterm infants will be reported to the DMC as rates and percent, stratified for treatment group.

*eSAE:*
Death before dischargeNecrotizing enterocolitis stage ≥ 2 or need for surgeryFocal intestinal perforationAny intraventricular hemorrhageAny intraventricular hemorrhage ≥ 3°Periventricular leucomalaciaAny persistent ductus arteriosus requiring treatment (medical/surgical)Any retinopathy of prematurity requiring treatmentRate of air leak syndromes (i.e., pneumothorax, pulmonary interstitial emphysema, pneumoperitoneum, pneumopericardium, pneumomediastinum)Rate of any air leak syndrome associated with any intraventricular hemorrhage

All other adverse events meeting the following criteria of seriousness will be considered unexpected serious adverse events and must be documented in the AE-from of the eCRF.

*uSAE* (any adverse event that resulted in any of the following):
DeathSerious deterioration in the health of the subject that resulted in any of the following:
Life-threatening illness or injury,Permanent impairment of a body structure or a body function,Medical or surgical intervention to prevent life-threatening illness or injury or permanent impairment to a body structure or a body function.

To ensure that there is no higher risk of deaths caused by the intervention, this will be evaluated with the help of 95% confidence limits that will be presented for both treatment groups. A DMC manual will describe the details of the safety analysis and has to be approved by all DMC members before preparing the first DMC report.

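### The primary composite omits death and does not say how an infant who dies within 120 h before meeting a failure criterion is classified

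*Protocol article*

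**What the plan says.** The endpoint is set out in Outcomes {12}: "The primary outcome is meeting one of the following treatment failure criteria", with a window of 120 h from birth. The criteria are invasive ventilation for more than 1 h; FiO2 of at least 50% for more than 1 h, counted only after NICU admission; and pCO2 "≥ 70 mmHg in two consecutive blood gas analyses > 2 h apart". Objectives {7} frames the hypothesis in the same terms, that higher PEEP "reduces the incidence of intubation and/or meeting predefined CPAP failure criteria within the first 120 h of life". The Methods part of the abstract and limitation (3) in the Discussion restate the endpoint. None of the four places names death.

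Death does appear elsewhere:

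- Adverse event reporting and harms {22} lists it as an expected serious adverse event and plans 95% confidence limits by group, introduced with "To ensure that there is no higher risk of deaths caused by the intervention".
- The discontinuation section {11b} names mortality as a reason to stop the trial.
- Table 1 schedules its assessment at 36 weeks' postmenstrual age and at the end of the study.
- Two secondary outcomes, the durations of ventilation and of respiratory support, run to 36 weeks or death.

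The intention-to-treat set in Statistical analysis {20a} "Consists of all patients included into the study of whom written parental consent was obtained and not withdrawn", so infants who die remain in it. The only provision for an unobserved primary endpoint is: "In case of more than 10% missing values concerning the primary endpoint, a worst case/best case analysis for this endpoint will be performed".

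**The concern.** Each criterion requires the infant to survive for some minimum time. Early death can therefore stop the endpoint from occurring, and under the definition as written the absence of a criterion means no failure. Any arm with more such deaths would gain apparent successes in the one confirmatory analysis. The article treats death as the end of follow-up for two secondary durations but makes no matching provision for the primary outcome. Adding a component to a confirmatory composite belongs in the endpoint definition, so this is not merely a detail for the analysis plan.

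**Working it through.** **Which deaths escape the criteria**

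| Situation | Ventilated > 1 h | FiO2 criterion | Two high pCO2 values |
|---|---|---|---|
| Death in the delivery room, not ventilated > 1 h | no | cannot count before NICU admission | not met if death precedes a second gas more than 2 h later |
| Death within 1 h of intubation, no earlier criterion | no | not met | not met |
| Death after redirection of care, no earlier criterion | no | not met | not met |

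These infants stay in the intention-to-treat set. If they were coded as missing instead, the worst/best case analysis would start only above 10% of 216 = 21.6, that is, from 22 infants. A few deaths would not trigger it.

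**The plan's own figure**

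Inputs from Sample size {14}: 50% versus 30%, level 0.05, power 80%. Two-sided testing is an assumption, because the article does not state sidedness.

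- Uncorrected: n = [1.960·√(2·0.4·0.6) + 0.842·√(0.5·0.5 + 0.3·0.7)]² / 0.2² = 93 per arm.
- Continuity-corrected: n = (93/4)·[1 + √(1 + 4/(93·0.2))]² = 102.8, so 103 per arm, as stated.
- With 5% dropout: 206/0.95 = 216.8 and 206·1.05 = 216.3. The stated 216 agrees within rounding.

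**Effect of adding death**

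The share of infants who die within 120 h with no criterion met is not given. I assume 0 to 3% per arm. Power is uncorrected, at 103 per arm.

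| Assumed share, low / high PEEP | Rates compared | n per arm (corrected) | Power |
|---|---|---|---|
| 0 / 0 | 50% vs 30% | 103 | 83.9% |
| 0.5% / 0.5% | 50.5% vs 30.5% | 104 | 83.8% |
| 1% / 1% | 51% vs 31% | 104 | 83.6% |
| 2% / 2% | 52% vs 32% | 105 | 83.4% |
| 3% / 3% | 53% vs 33% | 105 | 83.1% |
| 0 / 1% | 50% vs 31% | 114 | 79.8% |
| 0 / 3% | 50% vs 33% | 143 | 70.0% |

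In the last two rows power falls because the true difference in failure or death is smaller.

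**Effect of rescoring on the test**

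I take 216/2 = 108 per arm as one stratum. With a = control failures, m = all failures and N = 216, the Cochran-Mantel-Haenszel statistic without continuity correction is X² = (a − m/2)² / V, where V = 108²·m·(N − m) / [N²·(N − 1)].

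| Failures, low vs high PEEP | m | V | X² | p |
|---|---|---|---|---|
| 54 vs 39 | 93 | 13.30 | 7.5²/13.30 = 4.23 | 0.040 |
| 54 vs 40 (one high-PEEP death rescored) | 94 | 13.33 | 7²/13.33 = 3.67 | 0.055 |
| 55 vs 40 (one death rescored in each arm) | 95 | 13.37 | 7.5²/13.37 = 4.21 | 0.040 |
| 54 vs 32 (design effect, 50% vs 29.6%) | 86 | 13.00 | 11²/13.00 = 9.31 | 0.002 |
| 54 vs 34 (two high-PEEP deaths rescored) | 88 | 13.10 | 10²/13.10 = 7.63 | 0.006 |

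The boundary depends on the test form. With a continuity-corrected chi-square test, 39 versus 54 already gives p = 0.054.

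**The case against.** A reader might infer that the plan scores early deaths as treatment successes. The article does not say so. That result follows from the literal definition; coding such infants as missing is also open, and an analysis plan that is not shown could address it. What stands is that the published definition leaves the matter unsettled and that its plain reading gives a non-failure.

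The affected group is narrow. Most deteriorating infants would be ventilated for more than 1 h, or meet the FiO2 or pCO2 criterion, before dying. The gas criteria were added to capture infants in whom intubation is withheld, and infants with a palliative-only decision before study entry are excluded. Even death soon after intubation is arguable, since the first component speaks of need. This limits the size of the problem but leaves delivery-room deaths unclassified.

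A reader might also link the omission to air leak under higher PEEP. The Discussion addresses how often pneumothorax occurs, not death without prior ventilation, and nothing in the article shows how a fatal air leak would escape all three criteria. The documents do not support a forecast that the bias will favour high PEEP.

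Mortality is monitored: group-wise confidence limits are planned, safety reports go to the monitoring committee after 50, 100 and 150 infants, and mortality is a stated reason to stop. An excess of deaths would be seen beside the efficacy result, but this does not settle the efficacy classification.

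Finally, the hypothesis concerns respiratory failure on CPAP, and all-cause death brings some non-respiratory events into the composite. That is a real, small cost.

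**Conclusion.** The concern holds as a gap in the endpoint definition. Death is absent from all four statements of the primary outcome, no rule classifies an infant who dies within 120 h before meeting a criterion, and the literal reading makes that infant a non-failure in the intention-to-treat set. The bias would favour whichever arm had more such deaths.

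The likely effect is small and cannot be fixed from the article, which gives no early death rate. It would be wrong to conclude that the trial's result is likely to turn on this. The move from p = 0.040 to 0.055 needs a result exactly at the boundary, the rescored death in the high-PEEP arm, and an uncorrected test. With one death rescored in each arm, p stays at 0.040, and at the design effect two high-PEEP deaths leave the conclusion unchanged. The sample size of 103 per group is not in error. This is a change worth making because it is cheap and removes an avoidable ambiguity from the confirmatory endpoint.

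**What to change.** Add death from any cause within 120 h of birth as a fourth failure component in Outcomes {12}. Align the abstract, Objectives {7} and limitation (3) in the Discussion with it. Report each component separately by arm, so that deaths and respiratory failures can be told apart. Make the change before outcome data by arm are reviewed.

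The cost is one line in the definition and matching edits elsewhere. Death is already recorded, so no new data item is needed, provided that its timing relative to the 120 h window is captured. A few non-respiratory deaths will enter the composite. If deaths that meet no other criterion are balanced at an assumed 0 to 3% per arm, the required size moves from 103 to at most 105 per arm and power stays above 83%, so the planned 216 need not change on this account.

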**Methods:**

In this randomized multicenter trial, 216 preterm infants born at 26 + 0–29 + 6 gestational weeks will be allocated to receive a higher (6–8 cmH_2_O) or a lower (3–5 cmH_2_O) PEEP during neonatal resuscitation and the first 120 h of life. The PEEP level within each group will be titrated throughout the intervention based on the FiO_2_ (fraction of inspired oxygen concentration) requirements to keep oxygenation within the target range. The primary outcome is defined as the need for intubation and mechanical ventilation for > 1 h or being not ventilated but reaching one of the two pre-defined CPAP failure criteria (FiO_2_ > 0.5 for > 1 h or pCO_2_ ≥ 70 mmHg in two consecutive blood gas analyses at least 2 h apart).

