#### Interventional period

The intervention starts immediately after birth with the first application of nasal CPAP/NIPPV in the delivery room. The study intervention ends at a postnatal age of 120 h. Randomized subjects will receive nasal CPAP/NIPPV immediately after birth using a short nasopharyngeal tube, face mask, or binasal prongs (center specific). The PEEP level will be set within the allocated PEEP range: PEEP_low_ (3–5 cmH_2_O) or PEEP_high_ (6–8 cmH_2_O). During resuscitation, the *initial* PEEP setting in the intervention group must be set 3 cmH_2_O higher than in the control group and will be determined by center guideline prior to study start. The initial PEEP will be *maintained* during the delivery room management and will not be adjusted. Application of PEEP in the delivery room will be provided by a T-Piece resuscitator or a conventional ventilator. The use of a self or flow-inflating bag is not permitted for initial respiratory support. Subjects will be further resuscitated according to the European Consensus Guidelines [4]. Sustained inflation maneuvers can be applied according to local policies for initial stabilization. Primary nasal NIPPV (synchronized or not) can be used in the delivery room. After admission to the neonatal intensive care unit, the PEEP level will be adjusted according to the level of inspired oxygen required to meet the center-specific study SpO_2_ target range within the maximum range of 85–95% throughout the interventional period using the following PEEP titration protocol: (PEEP adjustments should be made on a half-hourly basis to allow the assessment of effects).

Prior to study initiation, we strongly recommend local guidelines for intubation and mechanical ventilation be defined, as well as the indication criteria for surfactant administration that have to be applied equally within both PEEP groups. Suggested intubation criteria within the study are:

FiO_2_ ≥ 0.5 for > 1 h and/or pCO_2_ ≥ 70 mmHg in two consecutive blood gas analysis > 2 h apart after the application of a maximum of 2 surfactant doses (either INSURE (intubate surfactant extubate) or less invasive, i.e., LISA).

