#### Continuous documentation of the study intervention

In both treatment groups, FiO_2_, set PEEP levels, and pressures during CPAP and NIPPV (mean airway pressure, peak inspiratory pressure, inspiratory time) will be recorded every hour throughout the interventional period on a worksheet and has to be signed by a study physician. All data will be transferred from hardcopy to electronic CRF files and are stored within the database of the center for pediatric clinical studies (CPCS), University of Tuebingen. This database fulfills all GCP and FDA CFR part 11 requirements. After termination of the study, all datasets are backed up within a locked area at the Justus-Liebig-University of Giessen and at the Eberhard-Karls-University of Tuebingen for at least 10 years after the end of the study.

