### Sample size {14}

Based on a pre-study survey among participating centers and the results of the AMV study [14], we expect 50% primary endpoints within the control group (lower PEEP level). The intervention will be regarded as being successful if it lowers the rate of the primary endpoints to 30%. This follows the expectations within similar studies [15]. To lower the rate of primary endpoints from 50 to 30% and to confirm this via Cochran-Mantel-Haenszel test (level of significance = 0.05, power = 80%), a sample size of 103 patients per group will be needed. To account for 5% drop outs, an overall sample size of 216 patients have to be recruited and treated within the study.

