
There are potential limitations in our study design that we addressed in the pre-study meetings: (1) all participating centers use nasal CPAP and NIPPV as primary respiratory support and post extubation. Because settings (inspiratory time, peak inspiratory pressure and respiratory rate) during NIPPV significantly affect the applied mean airway pressure and gas exchange, this could potentially result in unexpected and undesired differences in the study outcomes if this strategy is used unevenly between the two treatment groups. To resolve this issue, we decided that settings and weaning during the study intervention must be equally applied to both treatment arms in terms of inspiratory times, respiratory rate, and peak inspiratory pressures, which will be monitored and documented during the study intervention. The preparation of a center-specific protocol for the use of NIPPV prior to study initiation is strongly recommended and communicated during the pre-study meeting. (2) Analysis of the pre-study surveillance protocol revealed that participating centers use different modes of surfactant administration (INSURE or less invasive surfactant administration) as well as different thresholds and indications (FiO_2,_ pCO_2_, work of breathing) for surfactant administration. However, participating centers follow local guidelines ensuring that the indications and the mode of surfactant application are used similar between the two study groups within each center. (3) One of the primary endpoints is defined as need for intubation and invasive mechanical ventilation > 1 h. Although we strongly recommend that infants should be intubated if FiO_2_ ≥ 0.5 for > 1 h and/or pCO_2_ ≥ 70 mmHg in two consecutive blood gas analysis > 2 h apart after the application of a maximum of 2 surfactant doses, some physicians may however withheld intubation for any reasons. Therefore, we have chosen the criteria FiO_2_ ≥ 0.5 for > 1 h and/or pCO_2_ ≥ 70 mmHg in two consecutive blood gas analysis > 2 h apart after the application of a maximum of 2 surfactant doses as fulfillment of the primary endpoint as well (treatment failure). The abovementioned indicators for intubation (FiO_2_, pCO_2_) will be documented on an hourly basis. (4) Some physicians may have reservations against very high or very low PEEP settings that may lead to protocol violations. During the study preparation process and the pre-study meetings, there was a high agreement between the participating centers for the use of the two defined PEEP ranges. The ventilator parameters PEEP and FiO_2_ are recorded on an hourly basis to confirm protocol compliance or detect violence regarding the intended PEEP settings, which will then be discussed with the study monitor and the responsible investigator at the study site as soon as possible.

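### Read literally, the pCO2 limb of the primary endpoint cannot be met while gases are drawn every 2 h or less, and hourly FiO2 records misclassify some episodes of about 1–2 h

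*Protocol article*

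**What the plan says.** Outcomes {12} defines the primary outcome as any one of three failure criteria met "within the first 120 h after birth": invasive ventilation lasting more than 1 h after intubation; FiO2 of 50% or more for longer than 1 h after NICU admission; or pCO2 "≥ 70 mmHg in two consecutive blood gas analyses > 2 h apart".

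Other places word the same criteria, or their recording, differently:

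- **Abstract, Methods:** the gases are "in two consecutive blood gas analyses at least 2 h apart", and FiO2 must exceed 0.5 rather than reach it.
- **Discussion, limitation (3):** repeats the interval of more than 2 h and FiO2 of at least 0.5, and says that the indicators, naming FiO2 and pCO2, "will be documented on an hourly basis".
- **Continuous documentation of the study intervention:** FiO2, set PEEP and pressures "will be recorded every hour throughout the interventional period on a worksheet". pCO2 is not in that list.
- **Discussion, limitation (4):** PEEP and FiO2 "are recorded on an hourly basis to confirm protocol compliance". pCO2 is again not named.
- **Interventional period:** the suggested intubation criteria use the same gas interval, "in two consecutive blood gas analysis > 2 h apart after the application of a maximum of 2 surfactant doses".

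No section sets a blood gas schedule. None says how a gas drawn between two qualifying gases counts.

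**The concern.** Being consecutive and being more than 2 h apart are two conditions on the same pair of samples. Together they make the event depend on sampling frequency as well as on the infant's state: closer sampling of the same hypercapnia makes the criterion harder to meet.

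This matters for two reasons. Limitation (3) explains that the gas and FiO2 criteria were added to catch infants in whom intubation is withheld; for them the ventilation limb is silent and these limbs must work. And the intention-to-treat analysis of this endpoint is the only confirmatory analysis (Statistical analysis {20a}), in a trial whose clinical staff cannot be blinded (Who will be blinded {17a}).

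The FiO2 limb has a smaller problem: a threshold of more than 1 h is to be judged from records that are themselves 1 h apart.

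**Working it through.** The plan gives no figure for this point. The check applies the stated rules to sampling grids.

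**1. pCO2, one infant.** Suppose gases read 72, 75, 78 and 80 mmHg at 0, 1, 2 and 3 h. Adjacent gaps are 1, 1 and 1 h; none exceeds 2 h, so there is no event. Drop the gases at 1 and 2 h: the pair at 0 and 3 h has a gap of 3 h, so there is an event. The infant's course is the same and the classification is opposite.

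**2. How one extra gas removes an event.** Let two gases of at least 70 mmHg lie g hours apart, with g > 2. A further gas of at least 70 mmHg, a hours after the first, splits the gap into a and g − a. The event is lost if both parts are 2 h or less, which is possible only when g ≤ 4. Example: g = 3, a = 1.5 gives 1.5 and 1.5 h, and the event is gone unless another pair qualifies.

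**3. pCO2, regular sampling over 120 h.** Number of adjacent pairs = 120 / spacing.

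| Spacing (h) | Adjacent pairs | Gap > 2 h (Outcomes, Discussion) | Gap ≥ 2 h (abstract) |
|---|---|---|---|
| 1 | 120 | 0 | 0 |
| 2 | 60 | 0 | 60 |
| 2.5 | 48 | 48 | 48 |
| 3 | 40 | 40 | 40 |
| 4 | 30 | 30 | 30 |

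The literal rule switches from none to all as the spacing passes 2 h. At exactly 2 h the two versions in the article give opposite answers.

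**4. FiO2 from hourly entries.** For one unbroken episode, k consecutive entries at or above threshold are compatible with a true duration between k − 1 and k + 1 h: one entry with 0–2 h, two with 1–3 h, three with 2–4 h. If the episode lasts L hours (1 < L < 2) and starts at a random point between entries, two entries fall inside it with probability L − 1:

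| L (h) | Probability of two entries |
|---|---|
| 1.10 | 0.10 |
| 1.25 | 0.25 |
| 1.50 | 0.50 |
| 1.75 | 0.75 |
| 2.00 | 1.00 |

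A two-entry rule therefore captures every unbroken episode of 2 h or more and misses part of those between 1 and 2 h. A three-entry rule captures none below 2 h. Two entries are exactly 1 h apart, so they support a duration above 1 h only if FiO2 stayed at or above threshold between them.

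**5. Effect on event rates.** This would need the gas frequency, the share of events arising from each limb, and the lengths of FiO2 episodes. The article gives none of these. Sample size {14} assumes 50% against 30% for the composite as a whole. Its 103 per group is reproduced by a two-sided comparison of two proportions at 0.05 with 80% power and continuity correction, and nothing here changes it.

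**The case against.** The strongest reply is that the pCO2 limb fails only under a sampling pattern that the article never prescribes. That stands. The hourly statement in limitation (3) concerns documentation, and the section that lists the hourly worksheet leaves pCO2 out. A reader might infer that gases are drawn hourly and that the criterion can never be met; the document does not support this. A single adjacent pair more than 2 h apart, with both values at 70 mmHg or above, is enough.

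Second, the endpoint is a composite. An infant missed on pCO2 still counts if ventilated for more than 1 h or if the FiO2 limb is met, and limitation (3) strongly recommends intubating such infants. This also stands. It confines the loss to infants who meet neither other limb and whose gases during the episode are all 2 h or less apart.

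Third, unblinded care might suggest that the loss differs between arms. The route exists, but nothing in the article shows that gas frequency would differ, so bias by arm is a possibility and not a finding.

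Fourth, derivation detail may sit in the full protocol, the eCRF or the analysis plan, and source data remain at the sites. That weakens the FiO2 point, which concerns how a duration is derived. It does not answer the pCO2 point: the rule is stated in full, and it conflicts with the abstract. The word consecutive may have been meant as persistence over the interval, but the text does not say so.

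**Conclusion.** The pCO2 limb is badly fixed. Taken literally, it cannot be met in any period with gases at intervals of 2 h or less, and a confirmatory gas can cancel an event. This follows from the wording alone. How many infants are affected cannot be computed, and the sample size is untouched.

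Four inconsistencies need no assumption about sampling:

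- the gas interval differs between the abstract and both Outcomes {12} and the Discussion;
- the FiO2 threshold is strict in the abstract and inclusive in Outcomes {12};
- pCO2 is said to be documented hourly in one place;
- pCO2 is absent from the hourly worksheet in another.

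The first two are conflicts within the endpoint definition; the last two are the two sides of one conflict about recording.

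On FiO2, a reader might infer that hourly records cannot measure the criterion at all. They can: under a two-entry rule every unbroken episode of 2 h or more is found. The fault is misclassification of some episodes of about 1–2 h. The probabilities shown assume unbroken episodes, random onset, and the hourly entries as the only source.

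**What to change.** These changes concern endpoint derivation only.

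- **pCO2:** settle one interval and use it throughout. Count failure when two values of at least 70 mmHg are separated by that interval with no value below 70 mmHg between them. A further gas at or above 70 mmHg then cannot remove an event.
- **Data:** enter every blood gas with its time, to 120 h, in the eCRF.
- **FiO2:** settle one threshold. Record start and stop times of episodes at or above it, or fix one rule for hourly entries and state that it can miss episodes of 1–2 h. A two-entry rule is reproducible but keeps that gap.
- **Text:** reconcile the abstract, Continuous documentation of the study intervention, Outcomes {12} and limitation (3) of the Discussion. The matching wording in the suggested intubation criteria (Interventional period) is for the clinicians to reconcile; no clinical rule is proposed here.

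The cost is wording in the protocol, eCRF and analysis plan, and a small amount of extra transcription of gas and FiO2 times. The revised rule still needs two gases, so it does not remove all dependence on sampling; it removes the penalty for sampling more often.
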